### Investigational group

Participants randomized to the investigational group will be treated with high-dose rifampicin (body weight, dose: < 44 kg, 1200 mg/day; 45–54 kg, 1500 mg/day; 55–64 kg, 1800 mg/day; 65–74 kg, 2100 mg/day; > 75 kg, 2400 mg/day), isoniazid (300 mg/day), and pyrazinamide (body weight, dose: < 50 kg, 1000 mg/day; 50–70 kg, 1500 mg/day; > 70 kg, 2000 mg/day) until culture conversion (liquid medium) is confirmed (Table 2). High-dose rifampicin and isoniazid will be administered until 12 weeks after the date of sputum culture negative conversion. The dosage of rifampicin will be maintained throughout the study duration. Ethambutol will not be included in the initial regimen to reduce the number of pills. However, in the instance that isoniazid or pyrazinamide is discontinued prior to the end of treatment, ethambutol may be added to the treatment regimen if the investigator decides that reinforcement of the drug is necessary. Although temporary use of secondary anti-TB drugs is permitted in the case of adverse events such as liver toxicity, the total duration of use should be less than 4 weeks. If rifampicin is discontinued because of adverse events, the period of discontinuation must also be less than 4 weeks. The study overview is provided in Fig. 1.

**Table 2 Tab2:** Dose and schedule of anti-tuberculous drugs for the investigational group

Drug name	Dose (body weight)	Administration method
Isoniazid	300 mg/day	once a day before meal
Rifampicin	1200 mg/day (< 44 kg) 1500 mg/day (45–54 kg) 1800 mg/day (55–64 kg) 2100 mg/day (65–74 kg) 2400 mg/day (> 75 kg)	once a day before meal
Pyrazinamide	1000 mg/day (< 50 kg) 1500 mg/day (50–70 kg) 2000 mg/day (> 70 kg)	once a day after meal

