^h^ The EOT date is determined according to standard of care guidelines. A visit every 4 weeks until EOT and every 3 months after EOT. The test is not performed after EOT

^i^ If the 78-week visit (EOS) after randomization arrives earlier than the EOT + 9 M visit, the EOT + 9 M visit is omitted, and the EOS visit proceeds

**Table 4 Tab4:** Timeline for the investigational group

Type	Screening^a^	Baseline^a^	Treatment				End of treatment (EOT)^h^	Follow-up				End of study (EOS)
Visit name	Screening	D0	W2	W4	W6	W8	W12 ~ (Every 4 W)	EOT + 3 M	EOT + 6 M	EOT + 9 M	EOT + 12M^i^	M18^i^
Weeks (w)	− 14 ~ 0 days	0	2 W	4 W	6 W	8 W	12 W/16 W/20 W/24 W /28 W/32 W	EOT + 13 W	EOT + 26 W	EOT + 39 W	EOT + 52 W	78 W
Visit window	n-a	n-a	± 4 days	± 4 days	± 4 days	± 4 days	± 2 weeks	± 6 weeks	± 6 weeks	± 6 weeks	± 6 weeks	± 6 weeks
Consent	O											
Randomization		O										
Medical history	O											
Physical exam	O	O	O	O	O	O	O	O	O	O	O	O
Xpert MTB/RIF assay	O^e^											
Sputum AFB smear	O^e^	O^e^	O	O	O	O	O	O	O	O	O	O
TB culture (liquid)	O^e^	O^e^	O	O	O	O	O	O	O	O	O	O
DST^b^	With first/reverted cultured MTB											
Chest X-ray	O^e^	O^e^		O		O	O	O	O	O	O	O
Chemistry^c^	O^e^	O^e^	O	O	O	O	O^h^					
Complete blood count	O^e^	O^e^	O	O	O	O	O^h^					
HIV	O^e^											
Urine (or blood) HCG^d^	O	O	O	O	O	O	O^h^					
HBV/HCV^f^		O^e^										
Compliance of drug intake			O	O	O	O	O^h^					
Adverse drug reaction			O	O	O	O	O^h^	O				
Other medication^g^	O		O	O	O	O	O^h^					

^a^ It can be performed with the baseline visit if all screening results can be checked on the day

^b^ Drug susceptibility test for isoniazid, rifampicin, ethambutol, pyrazinamide, streptomycin, kanamycin, amikacin, capreomycin, ofloxacin, levofloxacin, moxifloxacin, prothionamide, cycloserine, rifabutin, and para-aminosalicylic acid (Omitted for the patients whose results are already reported)

^c^ Test items according to the standard treatment guidelines (refer to 6. Study procedures)

^d^ Performed for women of childbearing age tested within 7 days

^e^ The existing test results can be extracted and collected without additional testing if the previous test was performed within 4 weeks (based on the report day for the TB culture)

^f^ Since HBsAg and Anti-HCVAb are not excluded even if they are positive, drugs can be administered even before the results are reported

^g^ Confirmation of concomitant drugs, especially immunosuppressants including oral steroids

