^h^ The date of the end of treatment is determined according to the time of culture conversion to negative. A visit every 4 weeks until EOT and every 3 months after EOT. The test is not performed after EOT

^i^ If the 78-week visit (EOS) after randomization arrives earlier than the EOT + 12 M visit, the EOT + 12 M visit is omitted, and the EOS visit proceeds

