### Definitions

Culture of *M. tuberculosis* will be considered to be converted to negative when two or more consecutive cultures, taken at different visits, are found to be negative in liquid medium. When a participant cannot produce sputum after the first negative culture sputum, they will be considered as having achieved culture conversion. The submission date of the first confirmed negative sputum culture will be regarded as the date of culture conversion. If *M. tuberculosis* is found to be re-cultured two or more times following a negative culture conversion, this will be termed culture reversion [18]. Treatment success is defined as achieving negative culture conversion and maintaining negative cultures till the end of treatment.

The sum of treatment failure, recurrence, death during treatment (except for accidents and suicide), loss to follow-up, and withdrawal from the study will be designated as “unfavorable outcomes.” Treatment failure will be defined as participants who fail to achieve culture conversion during treatment period, or as participants using second-line anti-TB drugs for more than 4 weeks. Recurrence will be assigned to participants that indicate the presence of *M. tuberculosis* in sputum cultures for two or more times after the end of treatment.

Adverse events will be defined when undesirable medical events have occurred in participants, irrespective of a causal relationship with the treatment [19]. When adverse events result in death, life-threatening conditions, patient hospitalization or prolongation of existing hospitalization, persistent or significant disability or incapacity, or a congenital anomaly or birth defect, the events will be classified as serious adverse events. The severity of each adverse event will be assessed based on Common Terminology Criteria for Adverse Events (CTCAE) version 5.0 [20].

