### Statistical analysis

The results of this trial for outcomes will be analyzed based on intention-to-treat (ITT), modified ITT (mITT), and per protocol (PP) approaches, with a primary consideration for mITT results. The ITT group will include all participants who are randomized after satisfying eligibility criteria. The mITT group will include participants who are randomized and who have received the study drugs at least once. The PP group will include participants in the mITT group who have completed the standard treatment for at least 20 of the 24 weeks for the control group or those who have completed the planned treatment for at least 10 of the 12 weeks for the investigational group. A safety analysis will be performed based on the safety group, which will include participants who have been administered with at least one dose of the investigational drugs.

For the primary outcome analysis, the frequency of occurrence of unfavorable outcomes in the control and investigational groups will be analyzed, and the incidence rate of unfavorable outcomes ($${\widehat{P}}_{T}, {\widehat{P}}_{C}$$) and the 95% confidence interval will be estimated. In this non-inferiority test, if the upper limit of the two-sided 95% confidence interval of the difference in incidence of unfavorable outcomes at 18 months between the investigational and control groups ($${\widehat{P}}_{T}-{\widehat{P}}_{C}$$) is less than 6%, it will be concluded that the investigational group is not inferior to the control group.

For the analysis of time to unfavorable outcome, time to culture conversion, and time to recurrence, the median time of each group will be estimated using the Kaplan–Meier method and will be compared with the log-rank test. Treatment success rate and recurrent rate at the end of treatment will be compared with the chi-square test or Fisher’s exact test between the two groups.

Safety will be assessed based on the occurrence of adverse events during the clinical trial period. The frequency and proportion of all adverse events, serious adverse events, and adverse events of grade 3 or higher will be summarized and compared using the chi-square test or Fisher’s exact test.

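### Treatment success is defined by cultures alone, so a culture-negative participant with more than 4 weeks of second-line drugs is both a success and a treatment failure

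*Protocol article*

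**What the plan says.** All references are to the protocol article.

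- **Success (Definitions).** "Treatment success is defined as achieving negative culture conversion and maintaining negative cultures till the end of treatment". The sentence contains culture conditions only.
- **Conversion without sputum (Definitions).** "When a participant cannot produce sputum after the first negative culture sputum, they will be considered as having achieved culture conversion".
- **Treatment failure (Definitions).** Failure to convert during treatment, "or as participants using second-line anti-TB drugs for more than 4 weeks".
- **Unfavorable outcome (Definitions).** The composite adds up treatment failure, recurrence, "death during treatment (except for accidents and suicide), loss to follow-up, and withdrawal from the study will be designated as" unfavorable.
- **Short-term second-line use (Control group and Investigational group).** "Although temporary use of secondary anti-TB drugs is permitted in the case of adverse events such as liver toxicity, the total duration of use should" stay under 4 weeks.
- **End of treatment (Follow-up, note h to Tables 3 and 4).** Control: "The EOT date is determined according to standard of care guidelines". Investigational: "The date of the end of treatment is determined according to the time of culture conversion to negative".
- **Use of the definition (Study outcomes; Statistical analysis).** Success at the end of treatment is a named secondary outcome, and "Treatment success rate and recurrent rate at the end of treatment will be compared with the chi-square test or Fisher’s exact test". The primary outcome is the unfavorable proportion at 18 months.

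**The concern.** Success and treatment failure should exclude each other at the end of treatment. Here they are built on different axes. Success looks only at cultures. Failure looks at cultures or at drug use. Nothing in the success sentence refers back to failure, and no hierarchy says which label prevails when both apply.

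At stake is the meaning of a tested secondary efficacy outcome. A change of regimen driven by toxicity and lasting more than 4 weeks is a failure in the primary composite but leaves the success rate untouched. If such changes are more common in one arm, the comparison of success rates does not show it. The trial is open-label, so any case-by-case decision on these participants would be taken by people who may know the arm.

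**Working it through.** **1. The plan's own figure, to establish what is not affected.** Inputs from Sample size calculation: 10% unfavorable in both groups, margin 6 percentage points, one-sided 2.5%, power 80%.

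n per group = (1.960 + 0.842)² × [0.10 × 0.90 + 0.10 × 0.90] / 0.06² = 7.849 × 0.18 / 0.0036 = 392.4, rounded up to **393**.

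With 15% dropout: 393 / 0.85 = 462.4, rounded up to **463** per group, 926 in total. Both figures reproduce. They depend on the unfavorable-outcome proportion only, and the success definition enters nowhere.

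**2. The two definitions side by side.** Take a participant who has converted and has no later positive culture.

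| Course after conversion | Success? | Unfavorable? | Result |
|---|---|---|---|
| (a) Second-line drugs for more than 4 weeks, treatment finished | Yes | Yes (treatment failure) | Contradiction as written |
| (b) Second-line drugs for less than 4 weeks | Yes | No | Consistent |
| (c) Death (other than accident or suicide), withdrawal or loss during treatment | Yes if the end of treatment is the last dose; not shown if it is the planned end | Yes | Ambiguous |
| (d) Stops drugs early, stays in follow-up, no recurrence | Yes on the last-dose reading | No component met | Not counted both ways |
| (e) Recurrence, withdrawal or loss after the end of treatment | Yes, at that time point | Yes, at 18 months | Consistent, because the time points differ |

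Case (a) needs no special reading. Case (c) turns on how the end of treatment is understood for someone who never reaches it. Note h gives a rule for each arm, but neither rule mentions early leavers.

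**3. Effect on the success rate.** Let s be the share of an arm in case (a), plus case (c) if the last-dose reading is used. That arm's success rate is higher by s than under mutually exclusive definitions, and the between-arm difference shifts by s(investigational) − s(control). The document gives no value for s.

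For scale only, with assumed values: s = 1% gives 0.01 × 463 = 4.6, about 5 participants; s = 10% gives 0.10 × 463 = 46.3, about 46. The upper value equals the whole unfavorable proportion assumed for planning. Participants counted both ways at the end of treatment are a subset of the unfavorable ones, so under that planning assumption the true figure would be lower.

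**The case against.** The strongest reply is that the protocol sets the end of treatment by rule: 6 months in the control group and 12 weeks after conversion in the investigational group. On that reading, someone who dies or leaves at week 8 has not kept negative cultures to the end and is no success. This is a fair reading and it stands. A reader might infer that every converter who dies, withdraws or is lost is certainly scored both ways; the text supports only ambiguity.

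Other stronger inferences also fail:

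- **Early stopping.** Stopping drugs is not a component of the unfavorable outcome, so a participant who stops early and stays in follow-up is not counted twice.
- **Any switch to second-line drugs.** Use of less than 4 weeks is allowed and is not failure.
- **Success and unfavorable rates summing to more than 100%.** This can happen legitimately, because success is judged at the end of treatment and the composite at 18 months.
- **A large head count.** The Discussion cites 5.3% to 25.2% of Korean patients lost to follow-up. Counting half of the lower figure to all of the upper gives 0.5 × 5.3% × 463 = 12 to 25.2% × 463 = 117 per arm. Those are national figures, the count needs the disputed last-dose reading, and 117 is about 2.5 times the 46 unfavorable outcomes of all kinds that the plan's 10% implies.

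It is also said that outcome hierarchies are commonly left to the full protocol or the SAP. That would answer an omission. It does not answer case (a), where two definitions stated in the article conflict. Finally, the primary outcome and the time to unfavorable outcome do capture these events, so the harm is not hidden from the trial as a whole. That limits the consequence to one secondary outcome.

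**Conclusion.** The point holds in a narrow form. As written, a participant who converts, stays culture-negative and has more than 4 weeks of second-line drugs is a treatment success and a treatment failure at once, and the tested success rate includes that participant as a success. This follows from the two definitions alone.

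The status of converters who die, withdraw or are lost during treatment is unclear rather than wrong. It depends on whether the end of treatment means the planned end or the last dose taken.

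Only the secondary success rate and its between-arm comparison are affected. The non-inferiority test, the primary endpoint and the sample size stand. The number of participants concerned cannot be derived from the document; the 5 to 46 per arm shown above is an assumed range for scale, not an estimate. The correction is worth making because the outcome is named and tested, and the conflict is easily removed.

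**What to change.** In Definitions, replace the success sentence with one that requires:

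- culture conversion, and negative cultures up to the planned end of the assigned treatment in that arm;
- none of the following before that point: treatment failure (including more than 4 weeks of second-line drugs), death, loss to follow-up or withdrawal;
- all participants in the analysis set as the denominator, with mITT for the main result.

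Success and an on-treatment unfavorable outcome then exclude each other, while recurrence or loss after the end of treatment can still follow a success. The existing allowance for participants who cannot produce sputum need not change. A death from accident or suicide during treatment would be neither a success nor unfavorable under this wording, and the text should say so. The change does not add a course-completion requirement; completion stays in the per-protocol set (20 of 24 or 10 of 12 weeks).

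Cost: one sentence. The components are already needed for the primary outcome, so no new data are required. The downside is that reported success rates may be somewhat lower in both arms.

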### Control group

Participants randomized to the control group will receive standard treatment in accordance with the Korean guidelines for TB [17] and the World Health Organization guidelines [4]. Consequently, patients in the control group will be administered isoniazid, rifampicin, pyrazinamide, and ethambutol for 2 months, followed by isoniazid, rifampicin, (and ethambutol) for 4 months, comprising a total treatment period of 6 months (Table 1). Although temporary use of secondary anti-TB drugs is permitted in the case of adverse events such as liver toxicity, the total duration of use should be less than 4 weeks. If rifampicin is discontinued because of adverse events, the period of discontinuation must also be less than 4 weeks.

**Table 1 Tab1:** Dose and schedule of anti-tuberculous drugs for the control group

Drug name	Capacity			Administration method
	Per bodyweight	Recommended dose	Maximum dose	
Isoniazid	5 mg/kg	300 mg/day	300 mg/day	once a day before meal
Rifampicin	10 mg/kg	450 mg (< 50 kg) 600 mg (≥ 50 kg)	600 mg/day	once a day before meal
Pyrazinamide	20–30 mg/kg	1000 mg (< 50 kg) 1500 mg (50–70 kg) 2000 mg (> 70 kg)		once a day after meal
Ethambutol	15–20 mg/kg	800 mg (< 60 kg) 1200 mg (60–80 kg) 1600 mg (> 80 kg)		once a day after meal

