### Study outcomes

The primary outcome is the proportion of unfavorable outcomes at 18 months after randomization.

Secondary outcomes include time to unfavorable treatment outcomes, time to culture conversion on liquid medium, treatment success rate at the end of treatment, proportion of recurrence at 18 months after randomization, time to recurrence after treatment completion, and adverse events of grade 3 or higher during treatment.

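### The primary outcome is set at 18 months, but a death counts only during treatment, and treatment length differs by arm; the adverse-event window is also stated inconsistently

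*Protocol article*

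**What the plan says.** **Deaths.** The protocol article, Study outcomes, states: "The primary outcome is the proportion of unfavorable outcomes at 18 months after randomization". Definitions lists the components of an unfavorable outcome. The death component reads "death during treatment (except for accidents and suicide". The others are treatment failure, recurrence, loss to follow-up and withdrawal. Recurrence requires *M. tuberculosis* in two or more sputum cultures after the end of treatment.

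**Treatment length.** The Control group section describes a course "comprising a total treatment period of 6 months", and the per-protocol definition under Statistical analysis puts it in weeks ("at least 20 of the 24 weeks for the control group"). For the other arm, the Investigational group section says "High-dose rifampicin and isoniazid will be administered until 12 weeks after the date of sputum culture negative conversion", and footnote h of Table 4 confirms it: "The date of the end of treatment is determined according to the time of culture conversion to negative".

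**Adverse events.** Study outcomes names "adverse events of grade 3 or higher during treatment" as a secondary outcome. Statistical analysis says "Safety will be assessed based on the occurrence of adverse events during the clinical trial period" and compares crude proportions, including grade 3 or higher events, by chi-square or Fisher's exact test. Tables 3 and 4 schedule adverse drug reaction collection up to the visit 3 months after the end of treatment (EOT), and blood tests only up to EOT.

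**The concern.** The endpoint has one horizon for both arms, but its death component has a horizon set by the assigned regimen. If investigational treatment ends at week 16 to 20, a non-accidental death at week 22 is a primary event for a control participant and not a listed death event for that investigational participant. On average the asymmetry lowers the investigational rate. In a non-inferiority test that is the direction that makes a false claim easier.

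The recurrence component does not reliably catch these deaths. Post-treatment visits are 3 months apart with windows of plus or minus 6 weeks, so someone who stops, deteriorates and dies before two positive cultures are obtained meets neither definition. In a treatment-shortening trial that is an awkward gap, even if few participants fall into it.

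For adverse events the stakes are lower. The windows do not agree, and any window tied to EOT is shorter on average in the investigational arm.

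**Working it through.** **1. The plan's own sample size.** Inputs from Sample size calculation: 10% in both arms, margin 6 points, one-sided 2.5%, power 80%, dropout 15%.

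n = (1.960 + 0.842)² × 2 × 0.10 × 0.90 / 0.06² = 392.4, so 393 per group; 393 / 0.85 = 462.4, so 463 per group and 926 in total. Both figures reproduce.

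**2. Length of the death window.** Investigational window = conversion week + 12.

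| Conversion week | Investigational (weeks) | Shortfall vs 24-week control | Shortfall vs 26-week control |
|---|---|---|---|
| 4 | 16 | 8 | 10 |
| 8 | 20 | 4 | 6 |
| 12 | 24 | 0 | 2 |
| 14 | 26 | -2 | 0 |

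The window is shorter for conversion before week 12 (24-week control) or week 14 (26-week control), and equal or longer after that.

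**3. Shift in the risk difference.** The protocol gives neither mortality nor conversion times. Assumptions: constant hazard, equal in both arms; 18-month (78-week) mortality D of 2-5%; conversion at weeks 4-8; uncounted deaths stay in the denominator as not unfavorable. With h = -ln(1 - D)/78, the counted risk over w weeks is 1 - exp(-h·w). Shift toward the investigational arm, in percentage points:

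| D | Control 24 weeks (vs 20 to 16) | Control 26 weeks (vs 20 to 16) |
|---|---|---|
| 2% | 0.10 to 0.21 | 0.15 to 0.26 |
| 3% | 0.16 to 0.31 | 0.23 to 0.39 |
| 5% | 0.26 to 0.52 | 0.39 to 0.65 |

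The range is about 0.1 to 0.6 points. For scale, at D = 3% and a 26-week control course, 0.23 to 0.39% of 463 is about 1 to 2 deaths. With deaths counted to week 78 in both arms, equal mortality gives a shift of zero.

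**4. Effect on the error rate.** Suppose the true difference, with deaths counted to month 18 in both arms, equals the margin (10% vs 16%). A shift b makes the analyzed investigational rate 16% - b. Exact binomial probability that the upper limit of the unpooled (Wald) two-sided 95% interval lies below 6%:

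| b (points) | n = 393 per arm | n = 463 per arm |
|---|---|---|
| 0 | 2.6% | 2.6% |
| 0.35 | 3.7% | 3.7% |
| 0.5 | 4.2% | 4.3% |

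The normal approximation at n = 393 gives 2.5% with no shift and 4.0% at 0.5 points, so the result does not hinge on the method.

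**5. Adverse events.** Assumptions: equal constant weekly hazard and 20% with a grade 3 or higher event over 26 control weeks, so h = -ln(0.80)/26. Over 16 to 20 weeks, 1 - exp(-h·w) = 12.8% to 15.8%. Extending collection by 13 weeks in each arm gives 22.0% to 24.7% (29 to 33 weeks) against 28.4% (39 weeks). The gap narrows but does not close. A window of 18 months from randomization would be equal in both arms.

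**The case against.** **The effect is small and rests on assumptions.** This stands. Even 0.65 points is about 11% of the 6-point margin (0.65/6), and both mortality and conversion times are assumed.

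**Not every investigational participant has a shorter window.** This stands. Late converters are treated as long as controls or longer, and visits are scheduled to week 32. The claim concerns the average and depends on how early conversion occurs.

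**A reader might infer that relapse after early stopping, or all death from relapse, is left out of the primary outcome.** The text does not support that. Culture-documented relapse counts as recurrence whether or not the participant later dies, and cultures are scheduled every 3 months to month 18. Only a post-treatment death without two positive cultures escapes. Such a death might be recorded as loss to follow-up. The protocol does not say so, and listing death separately with a restriction points the other way.

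**A reader might also infer that grade 3 or higher adverse events are counted only on treatment, so the safety comparison is biased.** That goes too far. The statistical section uses the whole trial period and the visit tables run past EOT, so the fault is inconsistency. Fewer events over a shorter course is also partly the treatment effect the trial seeks: the Background names reducing adverse events as a reason for shortening. Comparing events per assigned course is legitimate, and the protocol gives no ground for making an early common window, such as weeks 0-12, the main comparison. The constant hazard in step 5 also overstates the gap if events cluster early.

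**Conclusion.** The death-window defect holds. It lies in the stated definition of the primary outcome, which conflicts with that outcome's own 18-month horizon, and on average it favors the shorter arm. Its likely size is 0.1 to 0.6 points, given equal 18-month mortality of 2-5%, conversion at weeks 4-8 and 24 to 26 control weeks. A shift of 0.35 to 0.5 points takes the false non-inferiority rate from about 2.6% to 3.7-4.3%. Any excess of deaths after early stopping is not in these figures. The defect is unlikely to decide the trial alone, but it should be corrected because it is systematic and cheap to remove.

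For adverse events, what holds is a three-way inconsistency of windows, plus the fact that any EOT-linked window is shorter on average in the investigational arm while crude proportions are compared. This is secondary.

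**What to change.** **Primary outcome.** In Definitions, count deaths from randomization to month 18 in both arms, with the same accident and suicide exception. Both visit tables already schedule a week-78 visit.

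**Planning rate.** Check whether the 10% control rate includes post-treatment deaths; the protocol does not say. If it does not, the step 1 formula gives 427 per group at 11% and 461 at 12% in both arms, before dropout, against 393.

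**Safety.** State one window for grade 3 or higher events and make Study outcomes, Statistical analysis and Tables 3 and 4 agree with it. Beside the crude proportions, give exposure-adjusted rates (events per person-week on treatment) as a supportive analysis.

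**Cost.** Some unrelated deaths will enter the composite in both arms. Cause of death must be recorded to month 18 so that the exception can be applied; the tables schedule no adverse drug reaction collection after the visit 3 months past EOT, so this may need an added data item. The rest is wording and a few tables.
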